## Abstract

**Background:**

Mothers' knowledge about the infant's problems and will provide the necessary care can increase the mother's confidence in providing care for her infant and eliminate misconceptions in primiparous mothers. The present study will be conducted to evaluate the effect of educational support intervention including peer groups for infant care on the growth rates of infants, breastfeeding self-efficacy and quality of life of their mothers in Iran.

**Methods:**

This quasi-experimental study is an educational support intervention protocol for infant care which will be conducted in two phases. The educational support program will be designed in the first phase. The program includes educational sessions on breastfeeding, growth and development of infants and care for children under 1 year of age in a virtual group where a physician, a nurse, a midwife and a healthcare provider are also present. Using the opinions of the experts, the peer group will discuss various points and the research team will finalize the program based on priorities. The second phase of the educational intervention will be conducted experimentally as a pretest–posttest design for the intervention and control groups.

**Discussion:**

The present study will provide useful protocol about the effect of educational support intervention for infant care and the sharing of peer group experiences on infants' growth rates, breastfeeding self-efficacy, and quality of life of their mothers. The current educational package not only combines virtual education and peer experiences in strengthening the education of mothers, but also it can improve mothers' physical and mental health and reduce medical costs by using telephone follow-up in supporting of the mothers of infants.

*Trial registration:* Registration of this randomized control trial has been completed with the Iranian Registry of Clinical Trials, IRCT20210913052457N1, registered 9/10/2021, https://www.irct.ir/trial/59093.

## Background

According to global nutritional goals and policies, by 2025, the rate of exclusive breastfeeding at 6 months should reach at least 50% [1]. The amount of exclusive breastfeeding varies in countries and even in different regions of the same country, such that exclusive breastfeeding has been reported in Japan is 21% [2], India 7.8% [3], Canada 6% [4], and Ghana 6.51% [5]. In Iran, according to reports, exclusive breastfeeding is 22.7% in urban areas, and 24% in rural areas, which is significantly different from WHO goals [6]. As one of the most sensitive stages of life, infancy is a period that needs to be correctly known, and precisely cared. The maintenance and promotion of children's health as a vulnerable group has a special place in health services, improving the level of knowledge and removing the false beliefs of mothers in caring for infants will lead to an increase in mother's self-confidence [7]. 

According to many studies, paying attention to care in the first years of an infant's life is of particular significance [8]. Accordingly, to prevent underweight, interventional measures should be taken before the age of two [9]. The mother's satisfaction with the quality of the baby's nutrition is a predictive variable of the breastfeeding self-efficacy score [10], according to studies, the mean score of breastfeeding self-efficacy in a study in Iran was 47.01, and in another study, this rate was 48.1 [11, 12]. The responsibility of infant care since birth has been to a large extent on the shoulder of mothers. As such, raising the awareness of mothers, their empowerment and improving their quality of life are the main objectives of the healthcare system. Mothers may experience various physical and mental complications during childbirth and the postpartum period, which can affect the natural process, and quality of their life [9, 13]. Quality of life is a feeling of well-being that arises from satisfaction or dissatisfaction with various life aspects that are of great importance to the individual; it includes the areas of health, occupation, socio-economic, psychology and family, and is a significant healthcare measurement criterion [14]. Chen et al.'s study showed that the quality of life of mothers who used different breastfeeding patterns and had a breastfeeding duration of 6 months or more had higher quality of life, this rate is also reported to be higher in mothers who exclusively breastfeed for up to 6 months [15]. Given the fact that most postpartum problems related to mother and infant are solved easily and through education, paying attention to the method, content and modality of these educations seems to be important [16]. The creation of positive self-efficacy, especially self-efficacy in breastfeeding, seems to be a prerequisite for mothers' empowerment [17]. The continuation of breastfeeding is easier in mothers with high self-efficacy in breastfeeding. According to researchers, mothers with more successful breastfeeding will more successfully raise their children and will have a stronger sense of accepting their motherly role. Bandura believes that one's level of empowerment and self-efficacy can be improved by adopting appropriate educational strategies and interventions in acquiring the necessary skills, and knowledge [18].

Today, e-learning is used by patients as the main part of healthcare. E-learning has been introduced by the World Health Organization as an appropriate way of communicating with clients [19, 20]. While virtual space and direct education through telemedicine have an overt role in the health system, the role of covert education through other clients with similar health problems cannot be ignored. In education through the experiences of peers, simple and safe learning is created based on the similar features of the members of a group; in this method, clients share their healthcare-related experiences [21]. Additionally, peer groups are better able to encourage their peers to choose appropriate health behaviors; they are also able to share common strengths, weaknesses, and experiences [22]. The need of mothers for breastfeeding-related scientific information and caring for their infants in encountering misconceptions reveals the need for education on the key points [23]. The positive role of educational programs in improving breastfeeding outcomes has been confirmed in various studies. However, no study has hitherto investigated the effect of a virtual educational-supportive program of infant care by sharing peer experiences on the growth indicators of infants, breastfeeding self-efficacy and quality of life of mothers. Thus, the present study will be conducted to bridge this gap.

## Aim

This study seeks to design and implement an educational support program for infant care by sharing the experiences of peers, which will be able to affect the indicators of infant growth, breastfeeding self-efficacy, and quality of life of mothers.

## Research hypotheses

The hypothesis is that after the intervention, the mean scores of infant growth indicators, mothers' breastfeeding self-efficacy, and mothers' quality of life will increase compared to the control group.

## Methods

This clinical trial study is an educational support intervention protocol for infant care which will be conducted in two phases. The educational support program will be designed in the first phase. This program will be designed based on the review of previous studies and considering the opinions of the panel of experts in health education and promotion, pediatric nursing, and mother-infant health. The program includes educational sessions on breastfeeding, growth and development of infants and cares for children under one year of age in a virtual group where a physician, a nurse, a midwife and a healthcare provider are also present. Using the opinions of the experts, the peer group will discuss various points and the research team will finalize the program based on priorities. Reminder text messages will be sent to the participants to remind them of the educational program. The second phase of the educational intervention will be conducted experimentally as a pretest–posttest design for the intervention and control groups.

## Study site and population

This clinical trial study will be conducted at the health centers in Yazd, Iran. Mother-infant pairs living at Yazd will be recruited from three health centers in the upper, lower and center of the city will be included in the study and will receive primary health care related to their infants according to the intervention program (virtual group and expert and peer training). In this study, the control group will have the routine services of health centers. These services include visiting the health center in person and checking the growth and development of the infant and receiving care information from the health team members.

## Phase I: designing an educational-supportive program

The design of the intervention and the identification of the target audience in this phase will be based on the review of the texts and similar studies as well as the opinions of experts. The educational support program will include virtual training sessions on breastfeeding, growth and development of infants and care for children under one year of age in a WhatsApp group where a physician, a nurse, a midwife and a healthcare provider are among the members. Moreover, the experiences of the peers will be used through discussions and the exchange of information. The studied population will be mother-infant pairs less than one year of age referring to Yazd health centers. The researcher will receive the mothers' phone numbers through the Sib system and will call to the mothers, and hold a face-to-face meeting at the health center.

### Virtual educational support sessions

All mothers of the intervention group will join the WhatsApp group, which is managed by the researchers. Additionally, other members of the virtual group include a midwife, a nurse, a healthcare provider and a family physician for answering the specialized questions of the mothers. Accordingly, about their questions, the mothers will have access to nurses, physicians and midwives.

In this group, 2 days a week, an educational program will be provided by the researcher in the form of educational packages related to breastfeeding, growth and development, vaccination, health and nutrition and other care for children under one year of age for two months. The educational content has been shown in Table 1. These packages will be sent to mothers based on the latest references from pediatric nursing books approved by the Ministry of Health and the family physician. Two days after sending the educational materials to the mothers, the researcher (pediatric nurse) will provide the mothers with additional explanations about the educational content for 40 min and the mothers will ask their questions. In this study, the control group will confirm the demographic information form and the consent form, and they will complete the quality of life and breastfeeding self-efficacy questionnaires before and after the intervention, and during the intervention, they will benefit from the routine services of health centers. These services include visiting the health center in person and checking the growth and development of the infant and receiving care information from the health team members.

**Table 1 Tab1:** Educational content

Educational program	Educational content	How to provide education	Audience
Educational package			
Newborn	Breastfeeding methods (time and duration of breastfeeding); milking and storing breast milk; bathing the infant; vaccination and aftercare; umbilical cord care; change of clothes; burping; methods of preventing sudden infant death syndrome; how to use supplements; Thyroid check-up (hypothyroidism training); education of danger and safety symptoms and the need for seeing a physician; and audiometry	The educational program will be offered two days a week and for two months in the form of an educational package which will be sent to the virtual group	Mothers of infants
One month to 1 year old	Optometry; complementary nutrition; toilet training; infant safety; food allergies; vaccinations and aftercare; weaning education; oral health of the infant; development of social skills as well as delicate and coarse movements		
Question and answer	Questions about the educational content and problems of the mothers and the response of the experts to these questions in the group	Necessary additional explanations about the educational content and questions asked by the mothers in the virtual group	Mothers of infants
Peer experiences	Sharing the experiences of mothers about the growth and development of their infants in a virtual group and under the supervision of experts	Sharing the experiences of mothers in a virtual group	Mothers of infants
Education follow-up	Message for reminding of educational content together with verbal encouragement	Sending reminder messages at the end of each week	

### Peer group experiences

In addition to virtual sessions, the mothers of this group will be able to share their experiences about the growth and development of their infants in this space for three months. At the beginning of the study, the mothers will be informed that the prescription of chemical, herbal, and traditional medicines is against the rules of the research plan and in case of violating these rules, they will be removed from the group. Sharing the experiences of mothers is limited to the issues of growth and development of a healthy child. The researcher and family physician will control all the messages of the intervention group members and prevent the mothers from confusion by providing them with correct guidance. Moreover, in case of illness and any clinical problems for the infant, it is recommended that mothers see a specialist in person.

### Follow-up and sustained education

For follow-up and sustained education, consolidate the educational content, at the end of each week, a summary of the taught content will be sent to mothers as a reminder. Also, to ensure the effectiveness of the training, at the end of each month, mothers will evaluate by answering questions about the content of the training materials.

### Expert’s team

The content and visual validity of the educational program will be measured, and the comments received from the panel of experts. The panel of experts will be included 4 professionals from the health education and health promotion field, 3 professionals from reproductive health and 2 experts from the field of pediatric nurses and a doctor.

## Phase II: implementation of educational intervention

In this step a randomized controlled clinical trial will be design to assess the efficacy of the prepared protocol. Participants will randomly be allocated into two groups. In the experimental group we will implement our designed protocol, and the control group will not receive any intervention, but they are evaluated as the same as the experimental group. For ethical issues all educational material will offer at the end of the study (Fig. 1).

**Fig. 1 Fig1:**
[figure not shown]
Flow chart of study design and population

### Study sample

This interventional randomized study will be conducted on mothers of infants who have been receiving maternity care at health centers in Yazd, Iran. According to the study of Araban et al. [24] and considering the level of significance (α = 0.05) and test power (β = 0.8) as well as the standard deviation of breastfeeding self-efficacy score which is 4.22 and 4.88 in case and control groups respectively, and in order to achieve a significant difference of at least 2.5 points in the mean score of breastfeeding self-efficacy in the intervention and control groups, and taking into account 10% of probable drop, the sample size is considered to be 57 subjects in each group using the following formula.$$n = \frac{{\left( {Z_{{1 - \frac{\alpha }{2}}} + Z_{1 - \beta } \left( {\sigma_{1}^{2} + \sigma_{2}^{2} } \right)} \right)}}{{d^{2} }}$$

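### The printed sample-size formula is wrong and gives about 6 per group, not 57; the standard formula comes close to 57, with about 78–79% power after the planned 10% loss

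*Protocol article*

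**What the plan says.** The Study sample section of the protocol article holds the document's only sample-size derivation. It fixes the error rates by "considering the level of significance (α = 0.05) and test power (β = 0.8"). It takes its variability from an earlier study, with a "standard deviation of breastfeeding self-efficacy score which is 4.22 and 4.88 in case and control groups respectively". The target is a "significant difference of at least 2.5 points in the mean score of breastfeeding self-efficacy in the intervention and control groups". It then concludes, "taking into account 10% of probable drop, the sample size is considered to be 57 subjects in each group using the following formula".

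The formula that follows reads, bracket for bracket:

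n = ( Z(1−α/2) + Z(1−β) (σ1² + σ2²) ) / d²

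No intermediate sample size is given, nor the method used to allow for drop-out.

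**The concern.** The text presents 57 as the output of the formula, and it is not. The usual formula for comparing two means squares the sum of the quantiles and multiplies that square by the sum of the variances. The printed one has no square, and its bracket attaches the variances to the power quantile alone. In addition, "test power (β = 0.8") uses the symbol for the type II error to denote power, and the formula then calls for Z(1−β).

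Formula, label and result therefore disagree in the one place where the size of the trial is justified. A reader cannot verify 57 from what is printed, and anyone who reused the formula would size a study at about one ninth of what is needed. A smaller question is whether 57 per group still gives 80% power once the expected 10% are lost. This matters a little more because the Data analysis section plans a per-protocol analysis, so losses come straight out of the analysed sample.

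**Working it through.** **Inputs, all from the Study sample section.** α = 0.05, two-sided because the formula uses Z(1−α/2), so Z = 1.960. Power is read as 0.80, so Z = 0.8416. SDs are 4.22 and 4.88, d = 2.5, drop-out 10%, equal groups.

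- Sum of variances: 4.22² + 4.88² = 17.81 + 23.81 = 41.62
- d² = 6.25

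**Can the stated 57 be reproduced?** With the standard formula:

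n = (Z(1−α/2) + Z(1−β))² (σ1² + σ2²) / d² = (1.960 + 0.8416)² × 41.62 / 6.25 = 52.27, so 53 evaluable per group.

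Allowance for 10% loss:

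| Route | Result |
|---|---|
| 52.27 × 1.1 | 57.5 |
| 52 × 1.1 | 57.2 |
| 52.27 / 0.9 | 58.1 |
| 53 / 0.9 | 58.9, so 59 |

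Either of the first two routes gives 57 when rounded down. The article does not say which was used, if either. Dividing by 0.9 is what offsets a 10% loss, and it exceeds the stated figure by 1 to 2 mothers per group.

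**What the printed formula gives.**

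| Version | Calculation | n per group |
|---|---|---|
| As printed | (1.960 + 0.8416 × 41.62) / 6.25 | 5.92 |
| Bracket corrected, still no square | (1.960 + 0.8416) × 41.62 / 6.25 | 18.66 |
| Square added, bracket left as printed | (1.960 + 0.8416 × 41.62)² / 6.25 | 218.9 |
| As printed, with β = 0.8 taken literally | (1.960 − 0.8416 × 41.62) / 6.25 | −5.29 |

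None of these becomes 57 through a 10% allowance, so both the square and the bracket must be corrected. The printed result is too small by a factor of 52.27 / 5.92, about 9.

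**Power with 57 per group.** The normal approximation is Φ(d / √(41.62/n) − 1.960).

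| Evaluable per group | Normal | t-test |
|---|---|---|
| 57 (no loss) | 83.3% | 82.7% |
| 51.3 (57 × 0.9) | 79.3% | 78.5% |
| 51 | 79.0% | 78.3% |

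With 51 per group, the difference detectable with 80% power is 2.8016 × √(41.62/51) = 2.53 points by the normal approximation and 2.56 by the t-test, against the planned 2.5.

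**The case against.** The strongest reply is that the trial's size is essentially right. The standard formula with the stated inputs comes within 1 to 2 mothers per group of 57, so the fault looks like one of transcription and not of design. Multiplying by 1.1 is a common convention for drop-out. The SDs come from one earlier study, and their uncertainty outweighs a power gap of one or two percentage points. The detectable difference moves by at most 0.06 points on a scale that runs from 14 to 70. All of this stands, and it is why the power shortfall is only a secondary note.

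It does not excuse the formula. The exponents on the variances and on d are printed correctly and the brackets are explicit, so the missing square cannot be put down to poor reproduction of the text.

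A reader might also infer more than the document supports:

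- **That the trial is materially underpowered.** It is not on its stated assumptions: 78–79% falls just short of 80%.
- **That the trial was planned with 20% power, because β is given as 0.8.** The same phrase calls the quantity power, and only the 80% reading leads to a figure near 57. It is a slip of notation.
- **That 57 is known to come from 52 × 1.1.** The article shows no such step, and 52.27 × 1.1 rounded down fits equally well.
- **That adjustment for baseline restores the power.** The Data analysis section names only paired t and Wilcoxon tests for the before-and-after comparison. It plans no baseline-adjusted comparison of the groups, and no pre–post correlation is given.

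**Conclusion.** The concern holds for the formula and the label. As printed, the formula gives about 6 per group and cannot be the source of 57, and power is mislabelled as β. The factor of about 9 measures the misprint, not the size of the trial.

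The sample size itself is close to what the standard formula requires: 53 evaluable per group, or 58 to 59 with strict allowance for 10% loss. Power for 2.5 points after that loss is about 79% by the normal approximation and 78% by the t-test. This is marginally below the stated 80% and of minor importance.

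These figures assume the SDs of 4.22 and 4.88, a two-sided 5% test, exactly 10% loss in each group, and an unadjusted comparison of the two groups' mean scores. With less loss the power target is met: with none, 57 per group gives about 83%.

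**What to change.** In the Study sample section:

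1. Print the formula as n = (Z(1−α/2) + Z(1−β))² (σ1² + σ2²) / d².
2. Write power (1 − β) = 0.80 in place of the β label.
3. Show the intermediate step: 52.3, so 53 evaluable per group before drop-out, and the method used to allow for drop-out.
4. Keep 57 per group and add a sentence such as: With 10% loss, about 51 mothers per group will be evaluable, which gives about 78–79% power to detect a 2.5-point difference in an unadjusted comparison between the groups.

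No power figure for a baseline-adjusted analysis should be added, since the protocol plans none.

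The cost is a text correction, with no change to recruitment or procedures. The price is that the stated power becomes slightly less favourable than 80%.

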### Sampling method

A random sampling method will apply to select the participants. The sampling method will be random and the participants will be in two groups’ intervention and control. The selection of participants to enter the study will be based on a table of random numbers, and to randomize the number of people in the control and intervention groups, cards will be prepared and placed in an envelope, then the participant will be asked to choose a card and based on the lottery will be placed in the control or intervention group.

### Inclusion criteria

Inclusion criteria include willingness to participate in the study, primiparous mothers, having an under one-year-old infant, physical health of the child and absence of chronic diseases and chromosomal-genetic defects, no underlying disease, access to mobile phones for connecting to virtual space, ability to use internet and media literacy. Iranian nationality, consent to participate in the study, ability to understand questions or literacy for reading and writing, and not participating in any other clinical trials at the same time.

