### Exclusion criteria

The diagnosis of chronic illness of the baby, the death of the baby, and the unwillingness of the mother to continue cooperation are the exclusion criteria.

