### Outcome measures

#### Breastfeeding self efficacy of mothers

The mean score of Breastfeeding Self efficacy of mothers will be measured using a questionnaire BSES-SF Dennis in the pre-test and post-test phases.

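### The trial is sized on breastfeeding self-efficacy, but the eligibility criteria do not require the mother to be breastfeeding, so the powered outcome may barely apply to some participants

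*Protocol article*

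**What the plan says.** **Eligibility.** Inclusion criteria: a primiparous mother "having an under one-year-old infant, physical health of the child and absence of chronic diseases", together with phone and internet access, literacy, nationality and consent. The Phase I section describes the same population: "The studied population will be mother-infant pairs less than one year of age referring to Yazd health centers". The Exclusion criteria section names only three grounds: chronic illness of the baby, death of the baby, and the mother's unwillingness to continue. Breastfeeding status appears in neither list.

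**Powered outcome.** The Study sample section derives 57 per group from the breastfeeding self-efficacy score alone, with SDs of 4.22 and 4.88, a difference of 2.5 points and 10% dropout, "considering the level of significance (α = 0.05) and test power (β = 0.8"). Under Outcome measures, "The mean score of Breastfeeding Self efficacy of mothers will be measured" with the BSES-SF before and after the intervention. The scale has 14 items and a range of 14 to 70.

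**Programme content.** In Table 1, breastfeeding technique and milk storage are in the newborn package. The package for one month to one year covers complementary nutrition and "weaning education".

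**Allocation and analysis.** Mothers are "recruited from three health centers in the upper, lower and center of the city". For allocation, "cards will be prepared and placed in an envelope, then the participant will be asked to choose a card". No balancing by infant age or centre is described. The Data analysis section names a paired t-test or Wilcoxon test and no covariates.

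**The concern.** The entry criteria and the outcome that determines the sample size do not fit together. Infants of any age under one year qualify, so some mothers may have stopped breastfeeding before enrolment. Such a mother would complete a scale on confidence in breastfeeding at both time points with little scope for the programme to change her score.

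What is at stake is power on the only outcome for which the trial was sized. The calculation assumes that the mean difference of 2.5 points applies to everyone analysed. If part of the sample cannot show it, either the mean difference shrinks or the usable sample does. As the working shows, the plan has no reserve to absorb this.

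A smaller, related matter is precision. Infant age plausibly bears on breastfeeding self-efficacy and spans a whole year, there are three centres, and neither the stated allocation nor the stated analysis takes account of them.

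**Working it through.** **Inputs from the Study sample section.** α = 0.05, two-sided (the formula uses Z at 1 − α/2); power 0.80 (printed as β); SDs 4.22 and 4.88; difference 2.5; dropout 10%; 57 per group.

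**Reproducing 57.** The printed formula does not square the sum of the Z terms and as printed does not give 57. In the standard squared form:

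n = (1.960 + 0.842)² × (4.22² + 4.88²) / 2.5² = 7.849 × 41.62 / 6.25 = 52.27

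Adding 10% gives 52.27 × 1.1 = 57.5, or 52 × 1.1 = 57.2, which matches the stated 57. Rounding up to 53 and dividing by 0.9 gives 59. The stated figure is reproduced, and the missing square is not relied on here.

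**Starting power.** After 10% loss, 57 × 0.9 = 51.3, so 51 per arm. The standard error of the difference is √(41.62 / 51) = 0.903, and power = Φ(2.5 / 0.903 − 1.96) = Φ(0.807) = 79%.

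**Effect of mothers who are not breastfeeding.** Let f be their share. The article gives no value; the rates in its Background are for exclusive breastfeeding and do not estimate f. I take 10%, 20% and 30% as assumptions and treat two cases.

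(a) They stay in the analysis, show no effect, and the SDs are unchanged: power = Φ(2.5 × (1 − f) / 0.903 − 1.96).

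(b) They are left out of the self-efficacy analysis: 51 × (1 − f) per arm remain, and power = Φ(2.5 / √(41.62 / (51 × (1 − f))) − 1.96).

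| f (assumed) | (a) mean effect | (a) power | (b) n per arm | (b) power |
|---|---|---|---|---|
| 0% | 2.50 | 79% | 51 | 79% |
| 10% | 2.25 | 70% | 45.9 | 75% |
| 20% | 2.00 | 60% | 40.8 | 70% |
| 30% | 1.75 | 49% | 35.7 | 64% |

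**Enrolment per arm for 80% power, allowing 10% loss.**

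- Case (a), 52.27 / (1 − f)² rounded up, then divided by 0.9 and rounded up: 73, 92 and 119 for f = 10%, 20% and 30%.
- Case (b), 53 / (1 − f) rounded up, then divided by 0.9 and rounded up: 66, 75 and 85.
- At f = 0 both give 59.

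**Age balance under simple allocation.** If infant age were uniform over 0 to 12 months (assumed), its SD is 12 / √12 = 3.46 months. At 57 per arm, the standard error of the difference in mean age is 3.46 × √(2 / 57) = 0.65 months. A gap of at least 1 month would occur in about 12% of trials, and of at least 1.5 months in about 2%. This is ordinary chance variation, which covariate adjustment can handle.

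**The case against.** **The share is unknown, and zero response is an assumption.** Both are true. If few mothers have stopped breastfeeding, the loss is small, and some who have stopped may still shift their score. The figures are therefore a range over assumed shares, and the milder case (b) stands beside case (a). It would go too far to call the outcome meaningless for these mothers; not applicable or weakly responsive is as much as can be said.

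**Weaning in Table 1 does not show that weaned mothers are enrolled.** Correct. The same row lists toilet training, so the content is probably anticipatory. The point rests on the eligibility lists, not on the table.

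**An article condenses the full protocol.** This does not remove the point, because the article sets out both eligibility lists item by item, and the lists as stated do not fit the stated sample-size outcome.

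**Growth and quality of life are also aims.** The Aim and Research hypotheses sections name all three outcomes, and a mother who has weaned can contribute to the other two. This stands, and it is why the fix offers an alternative to a narrower population.

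**Stronger readings that the article does not support.**

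- *Age imbalance confounds growth.* Four of the five growth indices under Infants' growth status are already referenced to age.
- *The unstratified draw is biased.* Simple random allocation is valid; imbalance in age or centre is a matter of chance and precision. Stratifying 114 mothers by centre and age band would be a design preference.
- *The draw is open, uses one envelope for all centres, returns cards after each draw, yields unequal arms or leaves no record.* The Sampling method section says none of this, and such details are commonly left to a full protocol. No selection bias can be inferred from silence.

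**Conclusion.** The point holds for eligibility and power. Followed as written, the plan can enrol mothers to whom the only powered outcome applies poorly or not at all, and it starts from 79% power at 51 per arm with nothing in hand. At assumed shares of 10% to 30%, power falls to between 70% and 49% with these mothers kept as non-responders, or to between 75% and 64% with them left out.

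These figures assume a true effect of 2.5 points in breastfeeding mothers, the stated SDs, 10% loss and a between-arm comparison, as the sample-size formula implies. The figure of 57 is not itself wrong on its stated inputs.

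The lack of balancing or adjustment for infant age and centre is secondary. It costs precision and is no evidence of bias.

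**What to change.** Choose one of two routes.

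1. **Entry criterion.** Add current breastfeeding at enrolment to the Inclusion criteria. The sample-size inputs, and the 57 to 59 per arm that follow from them, stay as they are. The cost is slightly slower recruitment and a narrower population for growth and quality of life.

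2. **Analysis set.** Keep the wider population for growth and quality of life, define the self-efficacy analysis set as mothers breastfeeding at baseline, and restate the power. The cost is either lower power (case (b)) or more recruitment: 66, 75 or 85 per arm at assumed shares of 10%, 20% or 30%. Breastfeeding status must then be recorded at the pre-test. It should not be taken from the post-test, because the programme may itself affect whether a mother continues.

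On either route, state in the Data analysis section that the arms are compared on post-test self-efficacy with adjustment for baseline score, infant age and health centre, for example by analysis of covariance. This needs a change of wording and the recording of age and centre, and no additional participants.
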